## Methods

In the “REMOTE blood pressure monitoring in high-risk pregnant women — a randomised controlled trial” (REMOTE CONTROL trial), a pragmatic non-inferiority unblinded multicentre randomised controlled trial, we aim to determine whether remote BP monitoring in pregnant women at high risk for developing a HDP is as safe as conventional clinic BP monitoring. We will evaluate foetal outcomes as the primary outcome, in addition to maternal outcomes, patient satisfaction and the cost-effectiveness of this strategy. This study protocol follows the SPIRIT reporting guidelines [37].

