### Design and setting

The REMOTE Control trial will recruit patients across 3 metropolitan Australian teaching hospitals; Liverpool, Campbelltown and Bankstown Hospitals. Within these hospitals, women at high risk of developing a hypertensive disorder of pregnancy are referred to specialist obstetric medicine clinics, where their blood pressure is monitored regularly throughout their pregnancy, leading to an additional 6–8 clinic reviews. The non-inferiority trial will compare remote blood pressure monitoring with conventional clinic monitoring in a 1:1 allocation ratio.

The trial has been prospectively registered with the Australian and New Zealand Clinical Trials Registry (ACTRN12620001049965p) in October 2020. Ethics approval was granted by the South Western Sydney Local Health District human research ethics committee (SWSLHD HREC) in June 2021.

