### Sample size

The sample size calculation is based on the assumption that the composite foetal outcome will be equal in the remote BP monitoring and control groups: a non-inferiority trial. Prior data indicates that the rate of the composite foetal outcome is approximately 31.1%, drawn from a study previously undertaken in the local high-risk pregnant population [4]. Investigators made a reasoned choice about the acceptable difference in adverse foetal outcome and feasibility of the trial. As a result, the non-inferiority margin was defined as a 15% absolute increase or less in the remote BP monitoring group. With a one-sided α of 0.05, the study will achieve a power of 0.80 if 118 women will be included in each trial arm. Furthermore allowing for a 20% attrition rate, 260 participants will be needed in total, 130 participants in each arm.

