The dichotomous primary outcome will be analysed using a generalised linear model (with binomial distribution and log link), adjusting for minimisation variables, chronic hypertension and aspirin use. Treatment effects will be expressed as adjusted risk ratios with 95% CIs. The secondary outcomes that are binary will be analysed using the same methods described for the primary outcomes, with corresponding 95% CIs. For those secondary outcomes that are continuous, data that is normally distributed will be analysed with parametric tests and non-normally distributed data will be analysed with non-parametric tests. Significance will be set at 0.05 and adjustments for multiple comparisons will be made where comparing several groups.

Subgroup analyses will be undertaken on (i) variables used in the minimisation algorithm (i.e. hypertension type [chronic or gestational hypertension] and LDA use); and (ii) other variables of prognostic significance pre-specified as ethnicity, body mass index, prior severe hypertension in the index pregnancy, antihypertensive therapy at randomisation, gestational diabetes mellitus at randomisation, and smoking status at randomisation. Subgroup analyses will be limited to the primary outcome. Results will be presented as adjusted risk ratios with 95% confidence intervals. The results of subgroup analyses will be treated with caution and will be used for the purposes of hypothesis generation only.

Participants with missing primary outcome data will not be included in the primary analysis in the first instance. This presents a risk of bias, and sensitivity analyses will be undertaken to assess the possible impact of the risk. Sensitivity analyses will also be undertaken for the women who were randomised to the conventional care arm, who had a remote blood pressure monitor at home. A post-hoc analysis will be undertaken for aspirin compliance as a modifier based on PFA-100 levels.

Comparison of questionnaires will be made for each time point.

A’within trial’ economic evaluation will be conducted alongside the trial from a health sector perspective, and extending to patient and carer costs. This will combine three forms of complimentary economic analysis in a comprehensive approach.

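### The non-inferiority margin is an absolute 15-point difference, but the primary effect is planned only as a risk ratio, with no ratio margin or conversion stated

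*Protocol article*

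**What the plan says.** The Methods section calls the study "a pragmatic non-inferiority unblinded multicentre randomised controlled trial", and the primary outcome is a composite adverse foetal outcome.

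The Sample size section of the protocol article fixes the design on the absolute scale:
- Planning rate: "the rate of the composite foetal outcome is approximately 31.1" per cent.
- Assumed truth: "the composite foetal outcome will be equal in the remote BP monitoring and control groups".
- Margin: "the non-inferiority margin was defined as a 15% absolute increase or less in the remote BP monitoring group".
- Error rates and size: "With a one-sided α of 0.05, the study will achieve a power of 0.80 if 118 women will be included in each trial arm".

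The section Data handling, analysis and result reporting fixes the analysis on the ratio scale. The primary outcome goes into a "generalised linear model (with binomial distribution and log link"), adjusted for chronic hypertension and aspirin use, and "Treatment effects will be expressed as adjusted risk ratios with 95% CIs". The same section commits to CONSORT with its non-inferiority extension. That governs reporting and does not choose a scale. Nowhere does the article give a margin for the risk ratio or say how the ratio will be set against 15 points.

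**The concern.** A non-inferiority conclusion comes from comparing a confidence limit with a margin, so both must be on the same scale. Here the margin and sample size are on one scale and the primary estimate is on another. A risk-ratio interval does not by itself say whether an excess of 15 points has been excluded. That also depends on the control-arm rate and on a method of conversion.

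Whether remote monitoring is as safe for the foetus is the trial's main question. With no conversion fixed, the analyst could use the planning rate, use the observed control rate, or standardise the fitted model. These routes can give different verdicts on the same data. A choice made after the results are known is open to challenge, and some of the choices also give up planned power.

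**Working it through.** **Inputs.** From the Sample size section: rate p = 0.311 in both arms, margin 0.15 absolute, one-sided alpha 0.05, power 0.80, n = 118 per arm. From the analysis section: log-link binomial model, adjusted risk ratio. Control rates other than 31.1% are illustrative assumptions.

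**1. Which scale does 118 per arm come from?** On the risk-difference scale,

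n = 2p(1 − p)(1.645 + 0.842)² / 0.15² = 2 × 0.311 × 0.689 × 6.18 / 0.0225 = 117.8, so 118 per arm.

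The stated figure reproduces, so the trial is sized on the absolute difference.

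**2. What ratio does 15 points correspond to?** RR = (p + 0.15)/p.

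| Control rate | RR equal to +15 points | Points allowed by a fixed RR of 1.482 |
|---|---|---|
| 20% (assumed) | 0.35/0.20 = 1.75 | 0.20 × 0.482 = 9.6 |
| 31.1% (planned) | 0.461/0.311 = 1.482 | 15.0 |
| 40% (assumed) | 0.55/0.40 = 1.375 | 0.40 × 0.482 = 19.3 |

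No single ratio stands in for the absolute margin.

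**3. Power if the ratio were judged against 1.482** (a hypothetical rule, with true equality at 31.1%):

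- SE(log RR) = √[2 × 0.689 / (118 × 0.311)] = 0.194
- ln 1.482 = 0.394
- Power at one-sided 0.05 = Φ(0.394/0.194 − 1.645) = 0.65
- For 80% power, n = 2 × (0.689/0.311) × 6.18 / 0.394² ≈ 177 per arm

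The risk-difference criterion at the same n and alpha gives 80.1%.

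**4. How often would the two criteria disagree?** Simulation of 400,000 trials per setting, 118 per arm, true equality, unadjusted Wald limits, one-sided 0.05:

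| Control rate | Ratio margin | Risk difference passes | Ratio passes | Disagree |
|---|---|---|---|---|
| 31.1% | 1.482 | 79.9% | 64.4% | 15.5% |
| 20% (assumed) | 1.482, held fixed | 89.3% | 44.6% | 44.7% |
| 20% (assumed) | 1.75, reset to that rate | 89.3% | 69.4% | 19.9% |

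In these three settings the disagreement is almost always one way: the risk difference passes and the ratio fails. At 31.1% the reverse occurs in about 0.01% of trials. The reverse becomes visible only when 1.482 is held fixed at a higher control rate, in about 3% of trials at an assumed 40%.

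**The case against.** Four points can be made for the plan.

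- **The ratio can be converted.** The log-link model gives fitted risks in each arm, so a standardised risk difference with an interval can be obtained from the same model and data. This stands. A reader might infer that the planned analysis is incapable of testing non-inferiority, and that goes too far. What remains is that the article states neither this conversion nor any other.
- **A decision rule is detail for the SAP.** That is fair for the mechanics of the comparison. It does not excuse the conflict, because the article itself fixes the margin's scale, the model, the link and the effect measure. An SAP that followed the article faithfully would inherit the mismatch.
- **The power and disagreement figures rest on a rule nobody has proposed.** Correct. The article does not plan to judge against 1.48, so 65% is conditional on that conversion and is not the power of the trial as written.
- **A between-arm difference is used elsewhere.** The cost-effectiveness analysis needs the change in the primary composite outcome. That is an economic analysis and does not supply the non-inferiority test.

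A reader might also infer that the mismatch makes a false claim of non-inferiority likely. The figures do not show this. At the planning rate the ratio criterion is nearly always the stricter one.

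The use of 95% intervals against a one-sided alpha of 0.05 is a separate matter, and no figure here relies on it.

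**Conclusion.** The concern holds as a conflict between two stated choices: an absolute margin that also determines the sample size, and a primary effect expressed only as a risk ratio. The planned estimate is not directly comparable with the margin, and no route between them is specified.

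At the planning rate the demonstrated harm is an undefined decision scale and, under a 1.48 ratio margin, a loss of power from 80% to about 65%. The disagreement of about 16% at 31.1% assumes true equality, 118 analysed per arm and unadjusted limits. At an assumed 20% rate the figure is about 45% only if 1.48 is kept, and about 20% if the margin is reset to 1.75.

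This should be corrected before analysis, because the primary conclusion depends on it. That judgement rests on the missing decision scale and does not need the simulated percentages.

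**What to change.** State the adjusted risk difference (remote minus usual care) as the primary non-inferiority estimate. Obtain it by standardisation from the covariate-adjusted binary model, or from a binomial model with identity link. Declare non-inferiority only if its upper confidence limit at the stated one-sided alpha of 0.05 (the upper end of a two-sided 90% interval) is below +15 percentage points. Keep the adjusted risk ratio as a supporting summary.

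This puts the analysis on the scale for which 118 per arm gives 80% power. If a ratio is preferred as primary, a ratio margin has to be justified in advance and the trial re-sized: about 177 per arm for a margin of 1.48.

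The recommended change costs a revised paragraph in the analysis section or SAP and a few lines of code. It needs no extra data or participants.

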### Outcome measures

The primary outcome is perinatal mortality and morbidity, represented by a composite adverse foetal outcome. The composite adverse foetal outcome is defined as: perinatal loss (miscarriage, pregnancy termination, stillbirth or neonatal death), high-level neonatal care (admission to neonatal intensive care unit or special care nursery for > 48 h) or small-for-gestational age (birthweight below the 10th centile). All components of the composite outcome will be assessed separately individually as secondary outcomes. Other secondary outcomes will consist of maternal outcomes, feasibility and patient satisfaction, quality of life, healthcare utilisation and cost-effectiveness (Table 3).

**Table 3 Tab3:** Secondary outcomes

*General*
Rate of composite maternal complications (adapted from the International Collaboration to Harmonise Outcomes for Pre-eclampsia [40]: - Maternal mortality - Eclampsia - Stroke -Cortical blindness - Retinal detachment - Pulmonary oedema - Acute kidney injury - Liver capsule haematoma or rupture - Placental abruption - Postpartum haemorrhage - Raised liver enzymes - Haemolysis - Low platelets - Admission to the intensive care unit - Intubation/mechanical ventilation
Gestational age at delivery
Birthweight
APGAR scores at 1 min and 5 min
Neonatal seizures
Neonatal respiratory morbidity
Uncontrolled hypertension
Pregnancy prolongation
Rate of preeclampsia
Rate of induction of labour
Mode of delivery
Postnatal readmission rate
Second trimester mean systolic and diastolic BP
Third trimester mean systolic and diastolic BP
Postnatal mean systolic and diastolic BP
Mean systolic and diastolic BP obtained in clinic setting
Area under the BP curve
Proportion of readings within target (< 140/90 mmHg)
Episodes of severe hypertension > 160/100 mmHg
Time to medication institution (weeks’ gestation)
Number of medication dose escalations

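### One adjusted log-binomial risk ratio is prescribed for every binary secondary outcome, and it breaks down for rare outcomes when an arm has no events

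*Protocol article*

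**What the plan says.** Under Data handling, analysis and result reporting, the primary outcome is to be analysed with a "generalised linear model (with binomial distribution and log link), adjusting for minimisation variables, chronic hypertension and aspirin use". The effect measure follows: "Treatment effects will be expressed as adjusted risk ratios with 95% CIs". The next sentence carries the method over without exception: "The secondary outcomes that are binary will be analysed using the same methods described for the primary outcomes, with corresponding 95% CIs".

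Under Outcome measures, the composite has three components: perinatal loss, high-level neonatal care and small for gestational age. The article adds: "All components of the composite outcome will be assessed separately individually as secondary outcomes". Perinatal loss is one component with four event types in brackets: "perinatal loss (miscarriage, pregnancy termination, stillbirth or neonatal death"). Table 3 lists "Neonatal seizures" as an outcome in its own right. The severe maternal events appear there as items under "Rate of composite maternal complications".

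The Sample size section says that "the rate of the composite foetal outcome is approximately 31.1"%, and plans on 118 women per arm, or 130 after an allowance for attrition. It gives no rate for any single component or for neonatal seizures.

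**The concern.** A log-binomial risk ratio works well for an outcome seen in nearly a third of women. The same rule also covers outcomes that may occur a handful of times, or not at all, in either arm. An empty arm drives the log risk ratio to plus or minus infinity, and a Wald interval around it means nothing.

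The trial asks whether remote monitoring is as safe as clinic monitoring. Its composite counts a neonatal unit stay over 48 hours or a small baby equally with a death, and its margin is 15 percentage points. The composite could therefore meet the margin while losses differ between arms. The component analyses are where a reader would look for that. For the rarest of them the stated method may yield no usable effect estimate or interval.

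**Working it through.** **Inputs.** From the article: composite rate 31.1% in both arms, margin 15 points, one-sided alpha 0.05, power 0.80, 118 per arm, 130 per arm recruited, 20% attrition. Assumed, because the article gives none: true rates of 0.5% to 3% for a rare outcome, equal in the two arms.

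**The plan's own figure.** n per arm = (1.645 + 0.842)² × 2 × 0.311 × 0.689 / 0.15² = 117.8, so 118. This matches the article. The range of evaluable women used below is 104 (130 × 0.8), 118 and 130 per arm.

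**How often is an arm empty?** One arm of n women has no event with probability (1 − p)^n. At least one of two arms is empty with probability 1 − (1 − (1 − p)^n)². For p = 1% and n = 118: 0.99^118 = 0.306, and 1 − 0.694² = 0.518.

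| Assumed true rate | 104 per arm | 118 per arm | 130 per arm |
|---|---|---|---|
| 0.5% | 0.835 | 0.801 | 0.771 |
| 1% | 0.580 | 0.518 | 0.468 |
| 2% | 0.230 | 0.176 | 0.139 |
| 3% | 0.082 | 0.054 | 0.038 |

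Both arms are empty, at 118 per arm, with probability 0.306 at a rate of 0.5% and 0.093 at 1%. If the true rates were 1% in the control arm and 3% in the remote arm, the control arm would still be empty in 0.99^118 = 31% of trials. For the composite the risk is nil: even at 104 per arm, 0.689^104 is about 1.5 × 10⁻¹⁷.

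**What the stated model returns.** Log-binomial fits at 118 per arm (remote v control):

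- 3 v 0, unadjusted: log risk ratio 21.7, standard error about 18,000, so z is about 0.001 and p = 0.999. With two binary covariates: 21.5, standard error about 16,000.
- 0 v 0: standard error about 33,000; no risk ratio is identified.
- 3 v 2: log risk ratio 0.41, standard error 0.90, an ordinary result.

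All of these fits were flagged as converged. The exact values in the failed fits depend on where the iteration stops, but the failure does not.

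**What an absolute measure returns.** The Wilson 95% limits are 0.87% to 7.21% for 3/118 and 0 to 3.15% for 0/118. The Newcombe limits for the risk difference then follow.

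- 3 v 0: difference 3/118 = 2.54 points. Lower limit 2.54 − √((2.54 − 0.87)² + 3.15²) = −1.0. Upper limit 2.54 + (7.21 − 2.54) = +7.2.
- 0 v 0: −3.2 to +3.2 points.

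A Miettinen-Nurminen score interval for 3 v 0 is close to this: −0.7 to +7.2 points.

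**The case against.** The strongest reply is that a fallback for sparse data usually sits in the SAP, which is not shown. That is fair as to the missing fallback. It does not dispose of the stated rule, which names one method for all binary secondary outcomes and makes no exception. Any fallback would depart from that rule, and the article says that analysts are not blinded, so it should be fixed in advance.

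Several stronger readings are tempting, and the article does not support them.

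- *Every safety outcome is affected.* The rule governs binary secondary outcomes. Adverse events are collected with no model imposed, and the severe maternal events sit within a composite rate.
- *Stillbirth and neonatal death will each be modelled.* They are sub-items of perinatal loss. Analysing perinatal loss as one less sparse outcome would satisfy the text. Neonatal seizures needs no such reading.
- *Serious harms would go unquantified.* Nothing prevents counts per arm from being reported, and the article commits to CONSORT. A 3 v 0 split would be visible.
- *No finite estimate or limit exists whenever an arm is empty.* With no events in the remote arm only, the risk ratio is 0. Profile likelihood, which the article does not rule out, keeps one finite limit when only one arm is empty (3 v 0: lower limit 1.13; 0 v 3: upper limit 0.89).
- *An empty covariate level also destroys the treatment effect.* It does not. With 3 v 2 events and none in women not taking aspirin, the treatment log risk ratio was 0.40 with standard error 0.90. Only the covariate's own coefficient diverges.

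It is also true that no method is informative at such counts. But a wide interval that can be read is better than a p-value near 1 from a failed fit.

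**Conclusion.** The point holds in a limited form. The article fixes a method for all binary secondary outcomes that gives no usable maximum-likelihood log risk ratio or Wald interval when an arm is empty, and no estimate at all when both are. With about 104 to 130 women per arm, an empty arm is likely for any outcome with a true rate of about 1% or less, and uncommon at 3%. These rates are assumptions with no source in the article. The worst practical result is a 3 v 0 imbalance shown with p near 1 from software that signals no problem.

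The primary analysis and its conclusion are untouched. The matter concerns how a few rare outcomes are summarised, and it is worth correcting because the correction is cheap.

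**What to change.** In the analysis section (or the SAP, with the article's rule qualified to match), keep the adjusted log-binomial model for binary secondary outcomes with adequate events in both arms. The threshold is a judgement to set before outcome data are seen; at least 10 events in total and at least one in each arm would be one example. For sparser outcomes, and always when an arm has no events, report counts per arm and the unadjusted risk difference with a Newcombe, score or exact unconditional 95% CI, and name which one. State also whether the four event types within perinatal loss are analysed singly or together.

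The cost is a sentence or two and no new data. The small downside is that these sparse outcomes are not adjusted for the minimisation factors, which matters little at such counts.

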	**Definition**
**Inclusion criteria**	
Age ≥ 18 years	
Able to provide informed consent	
Able and willing to follow instructions for use of automated BP machine and app-based system	
Chronic kidney disease	Abnormalities of kidney structure or function (either reduced GFR < 90 ml/min/1.73 m^2^, albuminuria or proteinuria) present prior to pregnancy
Autoimmune disorder	Diagnosis of an autoimmune condition such as systematic lupus erythematosus prior to pregnancy
Type 1 or type 2 diabetes mellitus	
Chronic hypertension	Systolic BP > 140 mmHg or diastolic BP > 90 mmHg on at least 2 occasions prior to 20 weeks’ gestation
Previous pregnancy complicated by HDP or diagnosis of gestational hypertension this pregnancy	Previous HDP includes chronic hypertension, gestational hypertension, preeclampsia, or preeclampsia superimposed on chronic hypertension Gestational hypertension (Systolic BP > 140 mmHg or diastolic BP > 90 mmHg on at least 2 occasions after 20 weeks’ gestation)
Confirmation of viable intrauterine pregnancy on dating scan	
IVF pregnancy	
High-risk for developing preeclampsia on first-trimester screening	Reported risk of < 1:100 of developing preeclampsia on commercially available combined first-trimester screening tests
Before 28 weeks gestation	

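### The primary model leaves out baseline variables the protocol itself calls prognostic, and gestation at entry, so it forgoes a modest precision gain without reducing the stated 80% power

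*Protocol article*

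**What the plan says.** The relevant statements are in the protocol article.

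- **Primary model** (Data handling, analysis and result reporting). The composite is analysed by a binomial model with a log link, "adjusting for minimisation variables, chronic hypertension and aspirin use". The result is an adjusted risk ratio with a 95% confidence interval.
- **Variables called prognostic** (same section). The subgroup paragraph lists "other variables of prognostic significance pre-specified as ethnicity, body mass index, prior severe hypertension in the index pregnancy, antihypertensive therapy at randomisation", then gestational diabetes and smoking, both at randomisation. These analyses are limited to the primary outcome and are for hypothesis generation.
- **Minimisation** (Study population). The factors are chronic hypertension, centre and aspirin use.
- **Entry window** (Table 1). Women need a dating scan confirming a viable intrauterine pregnancy and must enrol "Before 28 weeks gestation". Type 1 or type 2 diabetes is one of the qualifying risk features.
- **Primary outcome** (Outcome measures). One component is "perinatal loss (miscarriage, pregnancy termination, stillbirth or neonatal death"; the others are high-level neonatal care and small size for gestational age.
- **Sample size.** "With a one-sided α of 0.05, the study will achieve a power of 0.80 if 118 women will be included in each trial arm". The inputs are a rate of 31.1% assumed equal in the two arms, and a margin of 15 percentage points.

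**The concern.** The protocol identifies six baseline variables as prognostic and then keeps all of them out of the one analysis in which prognostic information would sharpen the answer. Two more facts established at entry are also unused. One is gestation at randomisation, which can range from soon after the dating scan up to 28 weeks and determines how much of the period at risk of miscarriage or termination still lies ahead. The other is pre-existing diabetes.

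Any outcome variation these variables explain stays in the error of the non-inferiority comparison, so the confidence interval is wider than it needs to be. The choice is also hard to revisit. The protocol says that data analysts will not be blinded to allocation, so covariates chosen after the data are seen would carry little weight in a non-inferiority claim. The gain is usable only if the list is fixed beforehand.

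**Working it through.** **Inputs from the Sample size section:** event risk p = 0.311 in both arms ("composite foetal outcome will be equal in the remote BP monitoring and control groups"), margin 0.15 as an absolute difference ("the non-inferiority margin was defined as a 15% absolute increase or less in the remote BP monitoring group"), one-sided α 0.05 (z = 1.645), power 0.80 (z = 0.842).

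**Input not in the documents:** R², the share of outcome variance explained by the added covariates. It is assumed, mainly over 2 to 10%.

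**Step 1. Reproduce the plan's figure with no covariates.**

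n per arm = (1.645 + 0.842)² × 2 × 0.311 × 0.689 / 0.15² = 6.183 × 0.42856 / 0.0225 = 117.8, rounded up to 118. This matches the protocol.

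Power at 118: SE = √(0.42856 / 118) = 0.0603; 0.15 / 0.0603 = 2.489; Φ(2.489 − 1.645) = 80.1%.

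The stated 80% therefore takes no credit for covariate adjustment of any kind.

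**Step 2. Let added covariates explain a share R² of the variance.** The SE is multiplied by √(1 − R²), and the required n by (1 − R²).

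| Assumed R² | Power at 118 per arm | n per arm for 80% power |
|---|---|---|
| 0% | 80.1% | 118 |
| 2% | 80.8% | 116 |
| 5% | 81.8% | 112 |
| 10% | 83.6% | 106 |

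For R² = 5%: SE = 0.0603 × √0.95 = 0.0587; 0.15 / 0.0587 = 2.554; Φ(2.554 − 1.645) = 81.8%.

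**Step 3. Check by simulation.** There were 1,500 trials per scenario. Each compared a standardised risk difference using two covariates with one using those two plus six binary covariates, with assumed prevalences of 10 to 40% and assumed odds ratios of 1.2 to 2.5 each.

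- At 118 per arm the gain was about 1 to 3 points (odds ratios 1.5 and 2.0).
- At 104 per arm power went from 74.1% to 74.6% at odds ratio 1.2, and from 74.5% to 79.6% at odds ratio 2.5.
- With the weakest predictors the variance did not fall (ratio 1.02).

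Monte Carlo error is about 1 point per power figure, so small differences between scenarios should not be read closely.

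**Step 4. Can the stated model carry the extra covariates?** Expected events are 0.311 × 208 ≈ 65 at 104 per arm and 0.311 × 236 ≈ 73 at 118 per arm. In simulated trials of 208 women, the log-binomial model with eight covariates reached a valid converged solution in only 12 to 72% of trials, depending on the scenario. With two covariates it did so in 100%. Lengthening the covariate list without changing the fitting method would therefore be unsafe.

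**The case against.** The strongest reply is that nothing here is an error. Adjusting for the allocation factors and keeping other variables for exploratory subgroups is coherent and valid. Calling a variable prognostic does not oblige a plan to adjust for it, and a two-covariate model suits a log-binomial fit with 65 to 73 events. This stands to the extent that the current model is valid. It does not remove the point that the article fixes the covariate set, and does so without variables it calls prognostic.

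Several stronger readings are tempting, and the documents do not support them.

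- **That planned power is lost.** Step 1 shows it is not, because the 118 was computed unadjusted. What is forgone is a possible gain.
- **That the omission leaves the trial underpowered after attrition.** Taking 20% off 130 leaves 104 per arm and about 75.5% power (SE = √(0.42856 / 104) = 0.0642; Φ(2.337 − 1.645)). That shortfall comes from the attrition arithmetic, a separate matter. Adjustment alone would need R² of about 1 − 104/117.8 = 12% to make it good.
- **That aspirin use hardly varies and is a wasted covariate.** Early low-dose aspirin is described as standard care, but no uptake figure is given. The protocol also minimises on aspirin use and plans a subgroup by it, which suggests that it expects variation.
- **That late entry changes risk substantially.** The direction is plausible for miscarriage and termination. But a viable pregnancy must be confirmed before entry, loss is only one of three components, and no rate is given.
- **That chance imbalance biases the result.** It does not; the confidence interval already allows for it.

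**Conclusion.** The point holds as a missed efficiency gain of low to moderate importance. The primary model leaves out six variables that the protocol calls prognostic, and also gestation at randomisation and pre-existing diabetes, although these data are planned for subgroups or needed for eligibility.

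At 118 per arm the gain is about 0.7 to 3.5 power points for an assumed R² of 2 to 10%, and about nil if the predictors are weak. The size rests wholly on that assumption. The relevant R² is what the new covariates add beyond those already in the model. Antihypertensive therapy, for example, probably overlaps with chronic hypertension, which argues for caution at the upper end. The stated power of 80% at 118 per arm is unaffected.

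**What to change.** In the primary-model paragraph of Data handling, analysis and result reporting:

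1. **Pre-specify a short list of covariates** alongside the minimisation variables. One example is gestational age at randomisation and BMI (both continuous), antihypertensive therapy at randomisation, pre-existing diabetes, and smoking. The list is kept short because of the event count, and the investigators may prefer a different short list. What matters is that it is fixed before outcome data are examined.
2. **Estimate the effect by a logistic working model standardised over all women**, with a standard error that suits the standardised estimate. This can still yield the planned risk ratio, and also a risk difference if wanted, without the log-binomial convergence problem.
3. **Keep the currently stated model as a sensitivity analysis.**
4. **State a rule for occasional missing baseline values**, so that no woman drops out of the primary analysis for that reason.

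**Cost.** No new data collection is needed, but the primary estimation method does change, so this is more than adding names to a list. With treatment, chronic hypertension, aspirin use, centre (three hospitals, two terms) and the five examples (smoking as yes/no), the model has 1 + 1 + 1 + 2 + 5 = 10 coefficients for about 65 to 73 events. That is a reason not to add all the listed variables.
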